### Oxygen uptake

Oxygen uptake responses will be assessed using the maximal response (VO_2_ max) and dynamic response (oxygen kinetics).*Maximal response (VO*_*2*_*max)*: peak oxygen consumption will be measured using a graded exercise test using the Balke protocol [29] with concomitant recording of the electrocardiogram. During the pilot and feasibility analysis, this test was found to be better tolerated in the study population than the modified Bruce protocol. The treadmill test will be terminated if the participanti.Reaches his/her peak oxygen consumption or predicted maximum heart rateii.Indicates that he/she cannot continue the testingiii.Has systolic blood pressure (SBP) above 220 mmHg or diastolic blood pressure (DBP) above 100 mmHg oriv.Develops abnormal electrocardiographic changes [30].The anaerobic threshold will be estimated during the maximal exercise test using the ventilatory threshold (VT). The VT is the workload at which the rate of pulmonary respiratory minute ventilation abruptly increases non-linearly during a progressive exercise test [31]. The VCO_2_ versus time and ventilatory equivalents (VE) versus time plots (AD instruments, Metabolic Module) will be used to graphically determine the VT.*Dynamic response (oxygen kinetics)*: oxygen kinetics describes the rate at which the cardiorespiratory system is able to deliver oxygen to the skeletal muscle and the rate at which oxygen is consumed by skeletal muscle. The rise to steady state is described by a time constant. A slowed time constant is a marker of impaired oxygen delivery/extraction. It takes longer for an individual with a slowed time constant to reach steady state [22].

Using a gas analyzer, VO_2_ will be recorded every 10 s during a submaximal exercise (20 min of walking at a treadmill speed predicted to elicit 50% VO_2_max). To assess the uptake kinetics, the time constant of the rise in VO_2_ from rest to steady state VO_2_ will be calculated.

A total of 10 min of controlled recovery will be calculated following the submaximal exercise to assess the off kinetics. The first part of the recovery will comprise a 1-min and 30-s standing phase, during which the subject is required to remain motionless and upright on the treadmill. Immediately following this, the subject will be seated for 8 min and 30 s, on a chair placed directly behind them on the treadmill. This combination of a short period of standing followed by seated recovery is similar to the protocol used in previous studies [32, 33]. The starting point of the curve will be forced to equal the average VO_2_ over the final 3 min of exercise to minimize the influence of spurious breathing at the end of the exercise on the span of the recovery curve. Excess post-exercise oxygen consumption (EPOC) will be calculated as the total area under the curve and the time constant will be estimated [33]. The time constants for both on and off kinetics will be calculated as a mono-exponential function.

### Oxidative stress

Blood samples will be collected from the antecubital vein after a 12-h fast and a 48-h period of no exercise. All samples will be taken in the morning to avoid the confounding effect of diurnal variation in oxidative stress parameters [34]. All samples will be analyzed in duplicate and then averaged. Catalase (CAT), superoxide dismutase (SOD) and glutathione peroxidase (GPX) activity in the plasma will be assessed using a commercial kit (Cayman Chemicals, Item no. 707002, 706,002, and 703,102, respectively) at wavelengths of 540 nm, 340 nm, and 450 nm, respectively. The nitric oxide (NO) levels will be measured as nitrites, using the Griess reaction and the absorbance will be read at 540 nm (Cayman Chemicals, Item no. 780001).

### Cardiac autonomic function

Cardiac autonomic function will be assessed as follows:*Heart rate recovery (HRR)*: heart rate recovery is a measure of the rate of decline of the heart rate during the first few minutes after peak exercise [35]. The heart rate will be derived from a continuous record obtained via electrocardiography (ECG) with surface electrodes placed in a lead-II arrangement. Lead site preparation and placement will be standardized according to American Heart Association standards. HRR will be calculated as the absolute difference between the heart rate at peak exercise and the heart rate recorded at 1- (HRR_1min_) and 2- min (HRR_2min_) post-exercise.*Heart rate variability (HRV)*: ECG signals will be recorded for 20 min with the participant in the supine position before the graded exercise test. Participants will be instructed to close their eyes and avoid any bodily movement or conversation during recording. Since the breathing rate has been found to confound HRV, breathing pace will be controlled at 12 breaths/minute with a metronome. After recording, all data will be stored and analyzed offline. Analysis of HRV will be performed using a time series of the last 5 minutes selected from the 20-min recording [36]. Data will be visually and automatically inspected for ectopic beats (premature, supraventricular, and ventricular); there must be no more than 10% ectopic beats in each record to be included in the analysis. Time and frequency domain variables of the HRV will be analyzed through the detection of R waves. ADInstruments LabChart version 7.3.7 software with HRV Module version 1.4.2 using Weltch window (Power Lab 8 SP, AD Instruments, Australia) will be used as the data acquisition software for recording ECG data, which calculates the R-R intervals as the measure of the difference between successive beats. All data acquisition and post-acquisition analyses will be performed in accordance with the guidelines proposed by the Task Force of the European Society of Cardiology and North American Society of Pacing and Electrophysiology [37].

### Cardiometabolic risk factors

Cardiometabolic risk factors will be assessed as follows:*Glycemic and lipid profiles*: HbA1c will be measured using 2–3 mL of blood drawn from participants who have fasted at least 10 h from the night before. HbA1c will be measured using high-performance liquid chromatography (HPLC). The fasting blood glucose and lipid profiles (comprising total cholesterol, triglycerides, HDL-C and LDL-C) will be estimated from serum samples. Total cholesterol and triglycerides will be measured using enzymatic colorimetric methods with cholesterol oxidase-peroxidase amino phenazone phenol and glycerol-3-phosphate oxidase-peroxidase amino phenazone phenol. HDL-C will be measured using a homogenous enzymatic colorimetric assay. LDL-C will be calculated using the Friedewald formula.*Resting blood pressure*: SBP and DBP will be measured using a standard sphygmomanometer. The participants will be strictly prohibited from consuming any caffeinated products 30 min before measurements; also exercising and smoking will be prohibited for the same duration before measurements. The patient will remain in relaxed seated state for 5 min and the BP cuff will be placed on either the right or left arm of the patient with the BP recording visible on the display. A second recording of the patient will be taken after 2 min. If the measurements display a BP difference ≥ 5 mmHg, further readings would be obtained until there are two consecutive stable measurements. An average of the two stable measurements will be considered the final reading. Following a rest period of 1–2 min, a recording from the other arm will be taken. If there is a measurement discrepancy between the upper extremities, then the extremity with the highest measurement will be used for analysis.

### Body composition

Body composition is defined as the amount and distribution of fat mass relative to the lean body mass. The amount (percentage) of body fat will be estimated using skinfold measurements and the distribution of fat (visceral adiposity/central obesity) will be assessed using waist circumference and waist-hip ratio.

Body density will be calculated from skinfold measurements taken at three sites (the chest, abdomen, and thigh in men; the triceps, thigh, and supra-iliac area in women), using the equations of Jackson and Pollack, and the Siri equation will be used to convert body density to percent body fat. Visceral obesity is defined as a waist circumference > 88 cm in women and > 102 cm in men. Waist circumference will be measured using a tape placed horizontally at the mid-point between the iliac crest and the lower aspect of the floating ribs in the mid axillary line, at the end of a normal expiration. Hip circumference will be measured at its greatest gluteal protuberance.

#### Sample size calculation

The number of subjects was determined using Software G. Power 3.192. An effect size of 0.44 was obtained from the data relative to changes in maximum aerobic capacity in a study by Lambers et al. [38], which examined the effects of aerobic training on obesity and cardiovascular risk in T2DM. A priori analysis of sample size using the *F* test (repeated measures analysis of variance (ANOVA), within-between interaction) showed that the total sample size required would be 52 to have 95% power at effect size of 0.44 and alpha level of 0.05. Considering the dropout rate from a previous similar investigation [30], the total sample size obtained is 60 or 15 subjects per group, using the allocation ratio of 1 for the four groups.

### Data monitoring

The researchers recruiting, implementing, and assessing the intervention will update the research team monthly about the study progress. No interim analysis will be performed.

### Harms

Aerobic training is an evidence-based intervention for glycemic control in patients with type 2 diabetes mellitus. All training sessions will be supervised by a professional physiotherapist to prevent any episode of hypoglycemia. However, if the patients experience a mild drop in blood sugar, it will be managed by trained professionals (oral administration of glucose as per American College of Sports Medicine guidelines). The doses of exercise proposed are in accordance with the guidelines of a joint position statement by the American Diabetic Association and American College of Sports Medicine. All potential adverse effects and unintended effects of the intervention will be reported.

### Auditing

The research supervisor ([name]) will randomly perform undisclosed laboratory visits during two assessments and one intervention session to assess protocol fidelity.

#### Statistical analyses

The intention-to-treat (ITT) analysis set will include all subjects who were randomized to the study and received at least one session of training. The normality of distribution will be examined for all variables and those found to have a non-normal distribution will be log transformed for further analyses. One-way ANOVA will be used to compare the groups at baseline. To test for the differences between groups and across two assessments, 4 × 2 split-plot ANOVA with group (LILV, LIHV, HIHV, control), time (baseline, 12 weeks) and interaction effect (Group × Time) will be employed. If the main effect of a group is found to be significant, the Bonferroni test will be employed as post hoc analysis. The significance level will be set at *p* < 0.05.

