### Group allocation

Random allocation to one of the four groups will occur after confirmation of eligibility and baseline assessment. Blind allocation by a remote researcher will be performed using computer-generated random numbers. The concealment of allocation will be ensured by using sequentially numbered, sealed, and opaque envelopes.

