### Interventions

Herein, VO_2_Reserve (VO_2_R) = VO_2_max – VO_2_rest, calculated during the graded maximal test for each subject. Participants will be randomly allocated into one of the four groups:i.Low-intensity, low-volume training (LILV) 3 times/week performing treadmill walking at 50% VO_2_Rii.Low-intensity, high-volume training (LIHV) 5 times/week performing treadmill walking at 50% VO_2_Riii.High-intensity, high-volume training (HIHV) 5 times/week performing treadmill walking at 80% VO_2_Riv.Control group receiving counseling and dietary advice but no supervised exercise.

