### Ethics

The trial methodology has been designed to incorporate features that minimize bias in controlled trials: randomization, concealed allocation, specification of eligibility criteria, blinded outcome assessment, blinded analysis, and ITT analysis.

This protocol was registered at the Clinical Trials Registry of India (CTRI/2017/08/009459) and was prospectively approved by the Institutional Ethical Committee, Jamia Millia Islamia (Reference:17/9/43/JMI/IEC/2015).

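### The set called intention-to-treat requires at least one training session, a condition the control arm cannot meet, so it is at best a modified-ITT set with a one-sided exclusion

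*Protocol article*

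**What the plan says.** The Statistical analyses section of the protocol article states that the ITT set "will include all subjects who were randomized to the study and received at least one session of training". Membership therefore needs both randomisation and a first training session.

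The Interventions section describes the fourth arm as "Control group receiving counseling and dietary advice but no supervised exercise"; Participants and Procedures describe it in the same way. The Harms section says that every training session is supervised. A patient without supervised exercise therefore has no training session in the protocol's sense of the term.

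The same Statistical analyses section plans a "4 × 2 split-plot ANOVA with group (LILV, LIHV, HIHV, control), time (baseline, 12 weeks"), so control is one of the four analysed groups.

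On timing, the Group allocation section says: "Random allocation to one of the four groups will occur after confirmation of eligibility and baseline assessment". The Ethics section counts "blinded outcome assessment, blinded analysis, and ITT analysis" among the features that limit bias.

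**The concern.** The definition, the description of the control arm and the analysis model cannot all hold as written. A condition that can be met only by training does not define a population containing untrained controls.

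If the condition is silently limited to the training arms, a different problem remains. Randomisation precedes the first session, so a patient can be randomised, have full baseline data and never start. Such a patient leaves the set if allocated to training, but a control has no equivalent step to fail. Participants cannot be blind to their exercise arm (Study design names only the outcome assessor as blinded), and the commitment differs by arm: three or five sessions a week, at 50% or 80% of VO2 reserve. Not starting may therefore depend on the allocated dose, and comparing doses is the purpose of the trial.

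The set applies to every primary and secondary outcome. Readers are told that the trial has ITT protection which the definition does not provide.

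**Working it through.** **Inputs.** Sample size calculation: 60 patients, 15 per arm, four arms; 52 needed before dropout; no dropout rate printed. Interventions: no training sessions in control. Statistical analyses: the set definition and the 4 × 2 model.

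**Step 1: the plan's own figures.** The article gives "total sample size required would be 52 to have 95% power at effect size of 0.44 and alpha level of 0.05" for the "repeated measures analysis of variance (ANOVA), within-between interaction" test. With λ = f²·N·m/(1 − ρ), f = 0.44, N = 52, m = 2 and ρ = 0, λ = 0.1936 × 52 × 2 = 20.13. With 3 and 48 degrees of freedom the power is 0.964, and 52 is the smallest multiple of 4 that reaches 0.95. So 52 reproduces if the two measurements are taken as uncorrelated; the article does not state the correlation. The set definition does not affect this figure. It matters here only as the source of the implied dropout allowance: 60 − 52 = 8, and 8/60 = 13.3%.

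**Step 2: who is in the set.** Let x be the number randomised to training who never start.

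| Definition | LILV | LIHV | HIHV | Control | Total |
|---|---|---|---|---|---|
| All randomised | 15 | 15 | 15 | 15 | 60 |
| As written, literally | at most 15 | at most 15 | at most 15 | 0 | at most 45 |
| Condition on training arms only | 45 − x over the three arms | | | 15 | 60 − x |

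In the second row the control cell is empty. The 4 × 2 model shrinks to 3 × 2, the group degrees of freedom fall from 3 to 2, and no training-versus-control contrast can be estimated. This contradicts the model in the same section.

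In the third row the model can be fitted, but x patients are removed after randomisation from three arms and none from the fourth.

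**Step 3: how large x could be.** The article gives no value. The allowance of 8 covers dropout of every kind, and nothing says that any of it falls before the first session. If all 8 were training-arm non-starters, the set would lose 8 of 45 (17.8%) from training and 0 of 15 from control. If the 8 were spread evenly over the arms and all preceded the first session, the training loss would be 13.3% × 45 = 6. Both are illustrations, and x could also be 0. Each patient removed is 1/15 = 6.7% of an arm.

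**Step 4: interaction with missing data.** A two-timepoint split-plot ANOVA in its usual form needs both the baseline and the week-12 value. A control who leaves early therefore drops out of that analysis too, although still a member of the set. The asymmetry has its effect on non-starters who do return at 12 weeks, or wherever the analysis keeps patients with a missing week-12 value.

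**The case against.** Four points can be made for the plan.

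- **No analyst would drop the controls.** The ANOVA names control as a group, so the intended reading is evidently the lenient one. This stands. A reader might infer from the definition that the trial will discard its control arm (15 of 60 patients), but the rest of the section does not support that as a plan. The literal reading shows an internal contradiction in the wording and no more.
- **Randomised-and-started sets are a recognised convention.** They are, under the name modified ITT. The convention is easiest to defend when every arm has a first treatment to receive and starting does not depend on knowing the allocation. Neither condition is met here, and the article uses the unmodified name.
- **Non-starters may be few.** Patients are referred, consent and complete three days of baseline testing before allocation, which may make non-starting uncommon. That is reasonable, but the article does not quantify it in either direction.
- **This is a condensed article, and an analysis plan may exist.** That would excuse an omission. Here the set is stated explicitly, and the statement conflicts with other sections of the same article.

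**Conclusion.** The point holds as an error of definition and labelling with a possible effect on the comparison. As written, the set contradicts the four-group analysis. On the likelier reading it is a modified-ITT set with an exclusion that can affect up to three arms and never control. On neither reading is it the ITT analysis claimed in the Ethics section.

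Its numerical effect is unknown. The number of non-starters is not given, and the implied allowance of 8 of 60 is the only related figure. That allowance is not a forecast of non-starters, and the proportional figure of 6 of 45 is not an upper bound. A reader might also infer that the rule favours training by leaving fitter or more motivated patients in those arms. That is plausible, but nothing in the article shows it, so no direction is claimed.

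The conclusion assumes that counselling does not count as a training session; no text suggests that it does. The planned sample size is unaffected.

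**What to change.** Replace the definition with: *The ITT set comprises all randomised participants, analysed in the arm to which they were allocated, irrespective of the number of sessions attended.* Use this set for every primary and secondary outcome.

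That sentence does not by itself bring non-starters back into the analysis, so two additions are needed:

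1. Seek the 12-week assessment from participants who never start or who stop training, in the same way as from everyone else.
2. Use an analysis that keeps participants whose 12-week value is missing, for example a mixed model for repeated measures with baseline and week 12 both as responses, and state its missing-data assumption. The model retains these patients but cannot stand in for an unmeasured week-12 value, so the first addition matters more.

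Label any set based on session attendance as modified ITT or per-protocol, and keep it supportive. Make the change before the outcome data are analysed, through the amendment route that the article describes.

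The cost is a short amendment, some follow-up effort and a modest change of model, with no additional patients. The estimated effect may be slightly smaller if patients who did not train are kept.

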### Outcomes

The primary and secondary outcomes are listed in Table 2. All outcomes will be assessed at baseline and after 12 weeks of intervention.

**Table 2 Tab2:** Outcomes and criterion measures

Primary Outcomes	
Oxygen Uptake Response	
a) Maximal Response	Peak oxygen consumption
b) Dynamic Response	Time constant of rise to steady state (“on” kinetics) Time constant of recovery from steady state (“off” kinetics)
Oxidative stress	
a) Antioxidant enzymes	Catalase Superoxide dismutase Glutathione peroxidase
b) Reactive species	Nitric oxide
Cardiac Autonomic Function	
a) Resting	Heart Rate Variability Time-domain indices: AvgNN, SDNN, RMSSD, pNN50 Frequency-domain indices: Total power, LF, HF, LF: HF ratio
b) Post-exercise	Heart rate recovery at 1 (HRR_1min_) and 2 min (HRR_2min_)
Secondary Outcomes	
Cardiometabolic risk factors	
a) Glycemic control	Glycosylated hemoglobin Fasting blood glucose
b) Lipid profile	Total cholesterol High-density Lipoprotein Low-density Lipoprotein Triglycerides
c) Resting blood pressure	Systolic blood pressure Diastolic blood pressure
Body composition	
a) Body fat (%)	Percent body fat derived from sum of skinfolds
b) Central obesity	Waist circumference Waist-Hip ratio

*AvgNN* Mean of N-N intervals, *SDNN* Standard deviation of N-N intervals, *RMSSD* Square root of the mean squared differences between adjacent RR intervals, *pNN50* Percentage of interval differences of adjacent RR intervals greater than 50 milliseconds derived from differences between consecutive RR intervals, *LF* Low frequency power, *HF* High frequency power, *LF/HF ratio* Ratio of low and high frequency power

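### Adjusting the 12-week value for the baseline already collected would be more precise than the planned split-plot ANOVA, at a cost of one degree of freedom per model

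*Protocol article*

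**What the plan says.** The Statistical analyses section of the protocol article gives the purpose of the main analysis ("To test for the differences between groups and across two assessments") and sets out the model: "4 × 2 split-plot ANOVA with group (LILV, LIHV, HIHV, control), time (baseline, 12 weeks) and interaction effect (Group × Time) will be employed". Baseline enters that model only as one level of time. Its only other role is a between-group check: "One-way ANOVA will be used to compare the groups at baseline". Pairwise comparisons depend on a different term of the model: "If the main effect of a group is found to be significant, the Bonferroni test will be employed as post hoc analysis".

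The Outcomes section fixes two visits: "All outcomes will be assessed at baseline and after 12 weeks of intervention". The Group allocation section puts baseline before randomisation: "Random allocation to one of the four groups will occur after confirmation of eligibility and baseline assessment". The Sample size calculation section sizes the trial on the interaction ("repeated measures analysis of variance (ANOVA), within-between interaction") and concludes that "the total sample size required would be 52 to have 95% power at effect size of 0.44 and alpha level of 0.05". This total is then raised to 60, or 15 per arm, for dropout. The article describes no baseline-adjusted model.

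**The concern.** Every outcome has a value measured before randomisation, so each has a legitimate covariate at no extra cost. The split-plot interaction uses that value by subtracting it in full, which is the best use only when the regression of the 12-week value on baseline has slope 1. When the slope is lower, subtraction adds baseline noise to the comparison. It also over-corrects any chance difference between arms on that outcome, and such differences are to be expected with 13 to 15 patients per arm. The baseline ANOVA may reveal an imbalance but adjusts for nothing.

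The rule for opening the Bonferroni comparisons adds to this. The group main effect concerns the mean of the baseline and 12-week values, so half of what it compares was measured before any training. What is at stake is precision, and whether the pairwise dose comparisons are reached at all.

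**Working it through.** **Inputs.** From the article: four arms, two visits, f = 0.44, α = 0.05, N = 52 before dropout and 60 after. The correlation ρ is not given, so a range is assumed. Equal variance σ² at both visits is also an assumption.

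**The plan's own figure.** For the within-between interaction with m = 2 visits, λ = f²·N·m/(1−ρ), on 3 and N−4 degrees of freedom. At ρ = 0, λ = 0.44² × 52 × 2 = 20.13 and power is 96.4%. With N in multiples of four, 52 is the smallest total that reaches 95%. So the stated figure is reproduced at ρ = 0, a value the article does not state. At ρ = 0.5 the same formula gives N = 28.

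**Why the interaction is a change-score test.** For arms j and k, the interaction contrast is the difference in mean change between them. Its error term is the within-arm variation of the individual changes, on N−4 degrees of freedom. The F statistic is therefore that of a one-way ANOVA on change.

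**Relative variance.** Per patient, the change score has variance 2σ²(1−ρ) and the baseline-adjusted value has σ²(1−ρ²). The ratio is (1−ρ²)/[2(1−ρ)] = (1+ρ)/2. Estimating one slope multiplies this by 1 + 1/(N−6), which is 47/46 = 1.022 at N = 52.

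| ρ (assumed) | (1+ρ)/2 | × 47/46 | Fall in standard error |
|---|---|---|---|
| 0.3 | 0.65 | 0.66 | 19% |
| 0.5 | 0.75 | 0.77 | 12.5% |
| 0.7 | 0.85 | 0.87 | 7% |
| 0.8 | 0.90 | 0.92 | 4% |
| 0.9 | 0.95 | 0.97 | 1.5% |

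Break-even is at (1+ρ)/2 = 46/47, so ρ = 0.96. At the ρ = 0 that reproduces N = 52, the ratio is 0.50 × 1.022 = 0.51.

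**Chance imbalance.** If two arms differ by d at baseline, the expected 12-week difference without treatment is ρd, so the change contrast is displaced by −(1−ρ)d. With 13 per arm, the standard deviation of d is σ√(2/13) = 0.39σ. At ρ = 0.5, an imbalance of that size moves the change contrast by 0.5 × 0.39σ ≈ 0.20σ. Under a linear model, ANCOVA takes this out.

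**The group main effect.** A 12-week effect δ becomes δ/2 in the mean of the two visits, which has variance σ²(1+ρ)/2. The noncentrality is proportional to (δ²/4)/[σ²(1+ρ)/2] = δ²/[2σ²(1+ρ)], against δ²/[2σ²(1−ρ)] for the interaction. The ratio is (1−ρ)/(1+ρ), or 0.54, 0.33, 0.18 and 0.05 at ρ = 0.3, 0.5, 0.7 and 0.9.

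**Simulation check.** This used 13 per arm and 3,000 runs per setting, with an illustrative graded effect chosen to give the interaction about 74% power.

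| ρ | Interaction | ANCOVA | Group main effect |
|---|---|---|---|
| 0.3 | 74% | 91% | 46% |
| 0.5 | 74% | 86% | 31% |
| 0.7 | 74% | 81% | 17% |
| 0.9 | 74% | 75% | 9% |

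With no effect, the interaction rejected in 4.8% to 5.2% of runs and ANCOVA in 4.8% to 5.4%. These powers show the ordering of the tests; they are not estimates of this trial's power.

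**The case against.** The planned interaction test is unbiased over randomisation, holds its type I error and is the test on which the trial was sized. Nothing in that choice is false. All of this stands, and it is why the point concerns precision only.

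A reader might infer a large loss of power. If f = 0.44 is taken as an effect on the change score, then λ = 0.44² × 52 = 10.07 and the interaction has 73% power. ANCOVA then has 90%, 84%, 79% and 76% at ρ = 0.3, 0.5, 0.7 and 0.8 once the slope cost is charged. The article does not support that starting point, because its own calculation reproduces at 96.4%. With the change-score test held there, ANCOVA gives 99.7%, 99.2%, 98.2%, 97.6% and 96.9% at ρ = 0.3, 0.5, 0.7, 0.8 and 0.9, a gain of 0.4 to 3.3 percentage points. The 73% comparison is illustrative at most.

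A reader might also infer that ANCOVA rescues the intention-to-treat analysis from dropout. It does not, because a patient with no 12-week value is lost to ANCOVA just as to the split-plot ANOVA. The article gives no dropout rate; a loss of 8 patients is only inferred from 60 − 52.

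Finally, the article reports no repeatability for the enzymes, heart rate variability indices or time constants. A claim that ρ is moderate for them would rest on nothing in the document.

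**Conclusion.** The point holds as a free improvement in precision. For any ρ below about 0.96 at N = 52, adjusting for baseline gives a smaller variance than the planned interaction test. The gain is worthwhile if ρ is 0.5 or less (variance ratio 0.77 or lower), modest at 0.7 (0.87) and small at 0.8 or above (0.92 or higher). These figures assume equal variances at the two visits and a linear relation with baseline.

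Three limits apply. The equivalence with a change-score test is exact for Group × Time only, and not for the group main effect that opens the Bonferroni comparisons; that term dilutes the effect further. Adjustment deals with chance imbalance in the outcome's own baseline, not in other characteristics. The documents do not support calling the planned interaction test biased or invalid, and the stated sample size need not rise on this account.

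**What to change.** In the Statistical analyses section, make the primary model for each outcome an ANCOVA of the 12-week value on arm, with the same variable's baseline as covariate. Where a log transformation is planned, apply it to both values. Base the Bonferroni pairwise comparisons on the adjusted arm effect instead of the split-plot group main effect.

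A nearly equivalent option is a mixed model with both visits as responses and a baseline mean constrained to be common to all arms. It also retains randomised patients who have only a baseline value, which ANCOVA alone does not.

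The cost is a change of wording and one error degree of freedom per model, with no extra patients or measurements. The Protocol amendments section already provides for ethics committee approval and notice to the registry. The Data monitoring section rules out an interim analysis, so the change can be dated before any comparison of outcomes between arms.
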